5.3 Biological Sampling Procedures

Blood samples (up to 5 ml per participant per occasion) will be collected for the analysis of Brain-Derived Neurotrophic Factor (BDNF) as an exploratory biomarker and for tolerance and safety measurements. Additionally, we aim to collect one tube (5 ml = 10ml in total) of additional whole blood per occasion for future analysis.

BDNF samples will be taken at five key time points: (1) before treatment (baseline), (2) and (3) at first integration session after Psilocybin 25mg dosing, (4) at 5 weeks, and (5) during the 6-month follow-up. This ensures comprehensive longitudinal data collection.

Blood samples of glucose, kidney and liver status will be measured for safety and tolerance reasons. None of these blood samples are collected or stored.

All blood samples are done by a standard peripheral venous sampling method performed by a nurse at the research facility at the university hospital clinic for psychiatry at [name].

Procedures will be implemented to minimize discomfort during blood collection, such as using pediatric needles for younger participants when necessary. Blood collection and processing will follow standardized protocols to ensure sample integrity.

Handling, Storage, and Destruction of Biological Samples:

Blood samples taken for analysis of BDNF will be analyzed at the Wallenberg Neuroscience Center or Avdelningen för neurokemi, thereafter stored at Region Skåne Bio bank for maximum 10 years under secure conditions and in accordance with Swedish regulations and the protocol for “Följsamhet med regler för hantering av biologiska prov”.

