**Rationale for Composite Outcome:**
This composite endpoint captures both clinical (BMI, hospitalization) and patient-centered (symptom deterioration) measures, aligning with the study’s aim to evaluate the efficacy of psilocybin in reducing the risk of relapse during a critical recovery period.

- Time to **Response:**

A clinically significant improvement in weight and psychological symptoms during the treatment period.

**Criteria**: **BMI Increase**: ≥10% increase in BMI from baseline (e.g., BMI 16 → BMI 17.6) or reaching a BMI ≥18.5 if achievable within the study period.

- Time to **Remission:**

The achievement and maintenance of weight restoration and psychological well-being, with no significant symptoms of anorexia nervosa.

**Criteria**: **Weight Restoration**: BMI ≥18.5 sustained for at least four weeks, or a weight within 90-95% of ideal body weight adjusted for age and height.

- Changes in AN symptom severity (measured by the Eating Disorder Examination from baseline to primary endpoint and follow-up 6 and 12 months.

- Changes in well-being from baseline to primary endpoint and follow-up 6 and 12 month.

- Changes in personality traits from baseline to primary endpoint and follow-up 6 and 12 months

- Changes in brain resting state connectivity (measured by fMRI), and commonly used task-based fMRI paradigms from baseline to primary endpoint. The task-based paradigms will involve food-related conditions, commonly used in the population (Celeghin et al., 2023; Bronleigh et al., 2022) as well as established paradigms involved in processing reward anticipation (Knutson et al., 2000; Ventorp et al 2022)

- Changes in peripheral BDNF measured in platelet-poor EDTA plasma from baseline to primary endpoint.

5. Trial Design and Procedures

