**Preparation Phase**

- Preparation Session 1 & Baseline Assessment (Week 0): Psychoeducation about psilocybin, breathing and relaxation techniques, rapport-building with therapists, and discussion of expectations and concerns.
  Includes full baseline assessments (list provided as attachment to protocol:
  - Expectation of Treatment Scale (ETS-BF)
  - Readiness and Motivation Questionnaire (RMQ)
  - General Change Mechanisms Questionnaire (GCMQ)
  - Patient Health Questionnaire (PHQ-9)
  - Generalized Anxiety Disorder scale (GAD-7)
  - Eating Disorder Examination Questionnaire (EDE-Q )
  - Columbia-Suicide Severity Rating Scale (C-SSRS)
  - Brief Psychiatric Rating Scale – Extended (BPRS+)
  - Satisfaction With Life Scale (SWLS)
  - Positive and Negative Affect Schedule (PANAS)
  - Harmony in Life Scale (HILS)
  - Ten Item Personality Inventory (TIPI)
  - Honesty-Humility Scale (HH)EGON
- Visual size estimation (EGON)

Vital signs, ECG, blood glucose, urine drug screening, pregnancy test, fMRI, BMI and blood sampling for BDNF and safety labs are also conducted.

Preparation Session 2 (Week 1): Conducted 7–10 days after Preparation 1, and 2–3 days before psilocybin dosing.

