**Dosing and Integration Phase**

Dosing Session 1 (Week 1): Psilocybin 25 mg under therapeutic support with ECG, blood glucose and blood pressure/pulse monitoring.

Integration Session 1 (Day after Dosing 1): Reflection, fMRI, blood sampling (including glucose, liver, kidney, BDNF), and reassessments with RMQ, GCMQ, PHQ-9, GAD-7, C-SSRS, BPRS+, SWLS, PANAS, HILS, TIPI, ECG and blood pressure/pulse. Psychedelic Experience related scales; Altered States of Consciousness Rating Scale (5D-ASC), Mystical Experience Questionnaire (MEQ-4), Meaningful Life Experience Rating (MLE).

Integration Session 2 (Week 2): Continued psychological integration support.

Integration Session 3 (Week 3): Summary of first dosing experience and preparation for second dosing. A pregnancy test is performed.

Dosing Session 2 (Week 4): Second psilocybin 25 mg administration under identical conditions as first dosing session.

Integration Session 4 (Day after Dosing 2): Reflection, blood sampling (including glucose, liver, kidney, BDNF), and reassessments with RMQ, GCMQ, PHQ-9, GAD-7, C-SSRS, BPRS+, SWLS, PANAS, HILS, TIPI, ECG and blood pressure/pulse. Psychedelic Experience related scales; Altered States of Consciousness Rating Scale (5D-ASC), Mystical Experience Questionnaire (MEQ-4), Meaningful Life Experience Rating (MLE).

Integration Session 5 (Week 5): Final integration session and preparation for long-term follow-up.

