**Primary Endpoint Week 9**

Includes full safety and outcome evaluations:
- fMRI

- blood sampling (including glucose, liver, kidney, glucose, BDNF)
- Vital signs, ECG, U-tox

- BMI
- AE/SAE monitoring
- Readiness and Motivation Questionnaire (RMQ)
- General Change Mechanisms Questionnaire (GCMQ)
- Patient Health Questionnaire (PHQ-9)
- Generalized Anxiety Disorder scale (GAD-7)
- Eating Disorder Examination Questionnaire (EDE-Q)
- Columbia-Suicide Severity Rating Scale (C-SSRS)
- Brief Psychiatric Rating Scale – Extended (BPRS+)
- Satisfaction With Life Scale (SWLS)
- Positive and Negative Affect Schedule (PANAS)
- Harmony in Life Scale (HILS)
- Ten Item Personality Inventory (TIPI)
- Honesty-Humility Scale (HH)

- Visual size estimation (EGON)

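### Section 5.3 times the fourth BDNF sample at 5 weeks, but the BDNF endpoint and the visit schedule both need it at Week 9

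*Protocol*

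**What the plan says.** Four parts of the protocol bear on when BDNF is measured.

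- **Endpoint (section 4.4).** The secondary endpoint is "Changes in peripheral BDNF measured in platelet-poor EDTA plasma from baseline to primary endpoint".
- **Visit schedule (section 5.2).** The only visit that carries the primary-endpoint name is headed "Primary Endpoint Week 9", and its assessments include "blood sampling (including glucose, liver, kidney, glucose, BDNF". BDNF is also listed at baseline ("fMRI, BMI and blood sampling for BDNF and safety labs are also conducted"), on the day after each dosing session, and at 6 months. The week-5 contact is described only as "Integration Session 5 (Week 5): Final integration session and preparation for long-term follow-up", with no blood sampling.
- **Sampling section (5.3).** It opens with "BDNF samples will be taken at five key time points: (1) before treatment (baseline", ties the second and third samples to the first integration session after dosing, and ends with "4) at 5 weeks, and (5) during the 6-month follow-up". It labels BDNF exploratory, whereas 4.4 lists it among the secondary endpoints.
- **Efficacy measurement (section 8.1).** The same 5-week time point appears for BMI, between baseline and 6 months. Section 5.2 lists BMI at Week 9 and none at week 5.

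**The concern.** Section 5.3 is where laboratory and nursing staff would look for sampling instructions. It states a number of samples and numbers each one, so it reads as complete. A reader following it alone would draw blood at week 5, where the visit schedule has no draw, and would not draw BDNF at week 9, where the endpoint is evaluated.

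At stake is the one value that turns the baseline sample into the endpoint defined in 4.4. A plasma sample not taken at the right visit cannot be recovered later, and no analysis plan can supply it. Nothing in the supplied text says which section prevails when 5.2 and 5.3 disagree.

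**Working it through.** The plan gives no figure to reproduce here. The check is a side-by-side count of the BDNF occasions, reading the second and third samples in 5.3 as one after each dose.

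| Occasion | Section 5.2 | Section 5.3 |
|---|---|---|
| Baseline (week 0) | yes | yes |
| Day after dose 1 | yes | yes |
| Day after dose 2 | yes | yes |
| Week 5 | no blood draw listed | yes |
| Week 9 | yes | no |
| Month 6 | yes | yes |
| Total | 5 | 5 |

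**Step 1: is 5.3 adding a sample or moving one?** The lists share 4 occasions, and their union is 5 + 5 − 4 = 6. Each section specifies five, so 5.3 cannot be read as the 5.2 schedule plus one. The fourth draw sits at two different times.

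**Step 2: what would be available under 5.3 alone?** The endpoint needs baseline and week 9. The nearest samples in 5.3 are at week 5, which is 9 − 5 = 4 weeks early, and at month 6, which section 8.2 labels Week 24 and is 24 − 9 = 15 weeks late. The baseline-to-week-9 change could not be computed. Baseline, post-dose, week-5 and month-6 values would still exist.

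**Step 3: could 5 weeks mean week 9?** Section 5.2 has "Dosing Session 2 (Week 4"). Counted from that label, 4 + 5 = 9, and the conflict disappears. But 5.3 gives no starting point, the protocol numbers its weeks from baseline at week 0, and TAU participants have no second dose to count from.

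**Step 4: how firm are the week labels?** Section 5.2 puts the second preparation session 7–10 days after the first and 2–3 days before dosing, so dose 1 falls at 7 + 2 = 9 to 10 + 3 = 13 days. Adding the 4-week interval from the dosing-interval rationale in section 5.1 gives dose 2 at 9 + 28 = 37 to 13 + 28 = 41 days. Week 5 is day 35, so on these counts dose 2 comes after week 5, not at Week 4. Five weeks after dose 2 would then be 37 + 35 = 72 to 41 + 35 = 76 days, against day 63 for week 9. The reading in step 3 therefore works on the labels only. For the same reason, no firm number of weeks since dosing can be attached to a week-5 sample.

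**Step 5: is it isolated?** No. Section 8.1 uses the same baseline, 5-week and 6-month pattern for BMI, and 5.2 again has Week 9 and nothing at week 5. Two outcomes carry the same mismatch, which suggests a mislabelled visit rather than a rival plan.

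**The case against.** The strongest reply is that the protocol as a whole does plan the week-9 sample. Section 5.2 is the schedule of procedures. It names BDNF at Week 9, and it describes the 6-month visit as repeating the primary-endpoint assessments apart from fMRI, with BDNF included. Blood is drawn at Week 9 anyway for glucose, liver and kidney tests. The protocol also refers to an attached schedule of assessments, which is not in the supplied text and may settle the matter. This stands: data are lost only if a site follows 5.3 over 5.2, and the likeliest explanation is a labelling slip. It does not remove the need to correct 5.3.

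A reader might infer more than the documents support:

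- **That the BDNF endpoint has no planned data.** Section 5.2 plans it. The gap arises only under 5.3 alone, and then only for the week-9 value.
- **That the randomised BDNF comparison is lost.** Section 7.4 offers TAU participants the switch only after the six-month follow-up, so a randomised baseline-to-month-6 comparison survives. The mechanism objective in 4.2 extends to six months and could still be addressed.
- **That a pairing of BDNF with the week-9 fMRI is broken.** The protocol lists the two as separate outcomes and plans no paired analysis.
- **That a week-5 sample would fall one week after dose 2 instead of five, or that week 5 exists only in the psilocybin arm.** The first rests on week labels that the protocol's own day counts do not support. The second is an inference, because 5.2 does not separate visits by arm.

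**Conclusion.** The contradiction is real and can be verified from the text. Sections 5.2 and 5.3 agree on four of five BDNF draws and disagree on the fourth, which is the one that the endpoint in 4.4 requires. If 5.3 is followed instead of 5.2, the baseline-to-week-9 change cannot be computed. If 5.2 is followed, nothing is lost.

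This rests on counting weeks from baseline, as 5.2 does, and on the primary endpoint in 4.4 being the visit so named in 5.2. The attached schedule could not be checked.

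The severity is should-fix. It is an internal inconsistency affecting one secondary endpoint in a pilot whose primary endpoint is safety. The primary safety endpoint does not depend on it. The differing labels for BDNF (secondary in 4.4, exploratory in 5.3) are a smaller matter, best settled in the same edit.

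**What to change.** Make three edits to the text:

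1. In section 5.3, change the timing of the fourth BDNF sample from 5 weeks to the Week 9 primary-endpoint visit, and state that it applies to both arms.
2. In section 8.1, reconcile the 5-week BMI measurement with the Week 9 visit in 5.2.
3. Give BDNF one status, secondary endpoint or exploratory, in both 4.4 and 5.3.

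Check the attached schedule of assessments against the corrected text at the same time. The Week 1 and Week 4 dosing labels and the day counts and interval stated elsewhere in the protocol also need to be reconciled with one another; which of them is right is for the sponsor to settle.

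The cost is a few lines of wording. No extra sample or visit is needed, because the Week 9 draw is already in 5.2. The correction should be made before sampling, because a missed draw cannot be replaced.

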5.4 Start, End, Temporary Halt, and Early Termination

- Start of the Clinical Trial: Defined as the first visit of the first participant (screening visit).

- Temporary Halt or Early Termination: Will occur if significant concerns arise from the sponsor, monitoring oversight or Safety Review Committee (see 9.1).

***Halt and/or Early Termination Criteria***

Halt and/or Early termination may be initiated if any of the following occurs:

- Unacceptable or unforeseen safety concerns, including unexpected serious adverse reactions (SUSARs) or a pattern of adverse events suggesting increased risk.
- Insufficient recruitment, defined as fewer than 30% of the planned number of participants being enrolled within 18 months of trial initiation.
- Emerging external evidence (e.g. from other clinical trials or meta-analyses) indicating that the investigational product poses a significant safety risk or is no longer ethically justifiable to study.
- Ethical concerns raised by the Safety Review Committee, monitor oversight or regulatory authorities.
- Withdrawal of essential approvals, resources, or study drug availability.

In the event of early termination or temporary halt, all relevant regulatory authorities (including CTIS, Läkemedelsverket, and EPN) will be notified within 15 calendar days, as per applicable regulations. The reason for halt and/or early termination will be documented and explained in the final report.

Safety Review committee and monitor clearance will be required before resuming after a temporary halt not leading to and early termination.

- End of the Clinical Trial: When the last participant completes the last follow-up visit at week 52.

6. Subject Selection

6.1 Inclusion Criteria

- Diagnosis of AN per DSM-5, including AN in partial remission.

- Have experienced at least one period of weight restoration to a minimum BMI of 17 followed by subsequent weight loss.

- Age 16-35.

- BMI >16

- Stable contact with a psychiatric unit.

- Ability to provide informed consent.

6.2 Exclusion Criteria

- Psychosis, bipolar disorder, substance use disorder, family history of psychosis or bipolar disorder, refusal of birth control, lifetime psychedelic use.
- Cardiovascular conditions,
  - Resting systolic blood pressure >140 mmHg or diastolic blood pressure >90 mmHg at screening or baseline.
  - Clinically significant arrhythmias, tachycardia and QT prolongation.
  - History of stroke, myocardial infarction, or other significant cardiovascular events.
  - Seizure disorders or history of epilepsy.
- Diabetes mellitus, positive drug tests, suicidal intent, allergy or intolerance to drug content, blood or needle phobia.
- Metal pieces in the body (contraindicated by fMRI, assessed in each case by MR-technician)
  - Only for the MRI-part of the study
- Any other clinically significant medical condition that, in the investigator’s opinion, may pose a risk to the participant or interfere with study results.
- Care under the Swedish Compulsory Psychiatric Care Act (LPT).
- Ongoing treatment with medications that have clinically relevant 5-HT2A-receptor antagonistic properties and are therefore expected to directly block or substantially interfere with the pharmacodynamic effects of psilocybin. Such medications require an appropriate washout period prior to psilocybin administration, based on pharmacokinetic properties and clinical judgement. Medications without direct 5-HT2A-antagonistic effects are not excluded on this basis**.**
- Sustained weight restoration, defined as BMI > 21.0 for ≥ 6 consecutive months within the 12 months prior to screening, as documented in medical records.

6.3 Screening and Inclusion

- Potential participants will be screened by a psychiatric clinician appointed by the principal investigator to ensure eligibility and understanding of the study requirements. A brief telephone pre-screening is performed before the screening visit to avoid unnecessary visits for patients. This is conducted following verbal permission to access medical records and consent to a short pre-screening assessment. Screening blood tests may be performed to exclude common medical conditions and support eligibility assessment.

6.4 Withdrawal and Discontinuation Criteria

**Discontinuation from the Clinical Trial**

A participant will be discontinued entirely from the clinical trial (i.e., all further participation and follow-up will end) only under the following condition:

- Withdrawal of informed consent at any time, for any reason, without the need to justify.

**Discontinuation from the Intervention (Dosing)**

Participants may be discontinued from the intervention (i.e., psilocybin administration – first or second dose), without being excluded from the trial. Participants will be encouraged to continue with follow-up assessments unless they explicitly withdraw consent.

This approach allows for continued safety and data collection in accordance with the intention-to-treat principle.

Reasons for discontinuing intervention may include:

- Development or discovery of exclusion criteria after inclusion (e.g. new psychiatric diagnosis, pregnancy).
- Emergence of a serious adverse event (SAE) or medical condition that, in the investigator’s judgment, makes continued treatment unsafe.
- Initiation of treatment with medications prohibited according to the protocol, i.e. medications with clinically relevant 5-HT2A-receptor antagonistic properties.
- Failure to adhere to critical aspects of the study protocol (e.g. repeated missed visits, non-compliance with preparation, or safety procedures).
- Investigator decision in consultation with the medical monitor.

The reason for discontinuation is documented in the eCRF. Participants will be offered a final follow-up visit when appropriate.

- Non-compliance to fMRI will not lead to study exclusion nor discontinuation of the intervention.

7. Trial Treatments

7.1 Description of Investigational Medicinal Products

Psilocybin: 25 mg, administered orally in a controlled clinical setting with manual based psychological support. The time for dosing is 10am and the duration of the dosing session is approximately 6-8 hours.

**Packaging of Investigational Medicinal Product**

- The investigational medicinal product PEX010 (psilocybin 25 mg capsules) is manufactured and packaged by Psilo Scientific Ltd., Burnaby, BC, Canada.
- The product is packaged in high-density polyethylene bottles with silica desiccant and cotton to ensure stability and protection from moisture.
- Each bottle contains the required number of capsules per study protocol and is sealed with induction technology to prevent contamination.

**Labelling of the IMP**

- Labelling of the investigational medicinal product and auxiliary medicinal products will comply with the EU Clinical Trials Regulation (CTR No. 536/2014), Chapter X, Articles 66-67, Annex VI, Sections A to D. All text on label is in English.
- The label will include, at a minimum:
  - Study title and protocol number
  - Unique batch and lot number
  - Expiry date or retest date
  - Storage conditions
  - Statement indicating “For clinical trial use only”
  - Contact information for the sponsor
  - The required regulatory caution statements as per EU CTR and Swedish regulatory guidelines
- A sample of the label will be provided as an appendix to the clinical trial application.

**Storage and Handling of the IMP**

- The PEX010 psilocybin capsules must be stored in a temperature-controlled environment at 15-30°C, as specified in the Certificate of Analysis (COA)​.
- The product must be protected from direct light and moisture to maintain stability and integrity​.
- Storage conditions at each clinical site must meet GMP and GDP (Good Distribution Practice) standards, and IMP storage will be regularly monitored to ensure compliance.

**Transport and Distribution**

- The IMP will be imported by Oriola and distributed in compliance with EU GDP regulations.
- During transportation, the IMP must be maintained at the required 15-30°C temperature range using validated packaging solutions.

**Accountability and Documentation**

- Site personnel will document all IMP storage, dispensing, and destruction in an IMP accountability log.
- The investigational product will be dispensed only to authorized personnel and must be administered strictly per protocol.
- IMP reconciliation will be conducted at study closeout, and unused product will be returned or destroyed in accordance with regulatory requirements.

7.2 Auxiliary Medicinal Products

- None planned.

- In cases of significant distress or adverse reactions during dosing sessions, adjunctive medications such as benzodiazepines (e.g., lorazepam) may be administered at the discretion of the study physician. These instances will be documented and reported to monitoring oversight and safety monitoring committee.

7.3 Concomitant Use of Other Medicinal Products and Treatments

Concomitant use of psychiatric medications may be permitted if not listed below and if deemed safe by the principal investigator.

**Participants receiving ongoing treatment with antipsychotic medications or lithium will generally not meet the inclusion criteria for this study, as such treatments typically indicate psychiatric conditions that are exclusionary according to the protocol and/or involve pharmacological mechanisms that are incompatible with psilocybin administration.**

**In cases where the underlying diagnosis does not in itself constitute an exclusion criterion, and a participant is receiving a medication with clinically relevant 5-HT2A-receptor antagonistic properties off-label or for other non-exclusionary indications, the investigator may, together with the participant, carefully assess the feasibility of dose reduction or discontinuation. If dose reduction or discontinuation is not clinically appropriate or feasible, the participant will not be included in the study.**

**Tricyclic antidepressants (TCAs) exhibit clinically relevant 5-HT2A-receptor antagonistic properties. Ongoing treatment with TCAs is rare in the target population. In the rare event of TCA treatment, careful clinical assessment must be undertaken to evaluate the medical necessity and feasibility of discontinuation. If dose reduction or discontinuation is not clinically appropriate or feasible, the participant will not be included in the study.**

**Mirtazapine, which has pronounced 5-HT2A-receptor antagonistic effects, may be considered for gradual tapering and discontinuation prior to psilocybin administration. If dose reduction or discontinuation is not clinically appropriate or feasible, the participant will not be included in the study.**

**Antihistamines with 5-HT2A-receptor antagonistic properties will be assessed on a case-by-case basis. As these medications are typically prescribed on an as-needed basis, temporary discontinuation prior to dosing is generally feasible.**

**Selective serotonin reuptake inhibitors (SSRIs) and serotonin–norepinephrine reuptake inhibitors (SNRIs) do not exhibit direct 5-HT2A-receptor antagonism and are therefore not prohibited per se.**

